#### Baseline measures

Participants will be asked to complete baseline demographic and psychological measures with the assistance of student helpers. Participants will be required to complete a questionnaire comprising: (a) demographic and economic variables (age, gender, education level, marital status and living arrangement, household income); (b) psychological variables using validated self-report measures of risk perception, outcome expectancies, action and coping self-efficacies, action and coping planning, and intention, with Chinese versions of these measures have been validated and used in a previous study [23], while items of recovery and maintenance self-efficacy [24] will be translated and back-translated and validated into Chinese prior to the start of study; and (c) influenza prevention behavioral variables (i.e., washing hands, avoid touching eyes, nose or mouth, and facemask wearing) will also be provided. In terms of the hand washing behavior, two situation-specific questions will be asked including (a) return to home and/or elderly center after being out and (b) before touching food. In terms of the behaviors of avoid touching eyes, nose or mouth, we ask how many times that participants be aware of and successfully inhibiting themselves touching their eyes, nose or mouth before they have washed their hands, particularly after they have been touching other objects that might lead them to exposure risk (e.g., stair rails and bannisters, door handles, chairs and tables, safety rails on the MTR etc.). In terms of the facemask wearing behaviors, we ask participants their facemask wearing behaviors when (a) in direct contact with people, (b) in crowded places such as shopping malls and the MTR. Participants will be informed that they will receive telephone calls in three randomly-selected days in the following 9 days asking them to report whether they have conducted the three influenza prevention behaviors. Participants’ self-reported clinical influenza episodes as well as flu-like symptoms during the past 3 months will also be collected.

#### Telephone-delivered individual behavior initiation sessions

Participants in (a) “behavior initiation” and (b) “behavior initiation + behavior maintenance” intervention groups will receive telephone-delivered intervention sessions at weekly intervals throughout the course of behavior initiation for 3 months. The purpose of these is to serve to remind participants of their influenza prevention goal and their action plans to implement them, mainly focused on the motivational stage. The intervention sessions will be administered by telephone lasting 10 to 20 min, and will be audio-recorded with the permission from participants for fidelity checks. To the extent that participants will have talked about their appropriate influenza prevention goals in the goal setting, mental simulation, and action planning exercises, step-by-step personal instructions and feelings about pursuing their goal, and when and where they will pursue their goals. Participants in the control group will not receive the telephone-delivered intervention sessions. Part-time research assistants will be recruited to deliver the telephone intervention sessions appropriately 10–15 min. They were be trained by, and receive feedback from, the PI and project coordinator and practice with each other in simulated scenarios.

#### Telephone-delivered individual behavior maintenance sessions

Following the behavior initiation session, all participants will be asked to report the three influenza prevention behaviors via telephone calls in three randomly-selected days in 9 days, clinical influenza episodes as well as flu-like symptoms in the past 3 months, and then they will again be invited to complete the same set of psychological outcome measures administered at baseline. Thereafter that only participants allocated to the “behavior initiation + behavior maintenance” intervention group will continue to receive telephone-delivered intervention sessions at weekly intervals for 3 months. The sessions will focus on strategies of behavior maintenance at the volitional stage.

#### Follow-up measures

At the 3-month (i.e., the middle time point of the intervention after the behavior initiation session), 6-month (post-intervention), and 12-month follow-up occasions, participants will receive the same set of psychological outcome measures administered at baseline. They will also be asked to report the three influenza prevention behaviors (i.e., washing hands, avoid touching eyes, nose or mouth, and facemask wearing) as well as whether they get vaccinated via telephone calls in three randomly-selected days in 9 days. Participants’ self-reported clinical influenza episodes as well as flu-like symptoms during the past 3 months will also be collected. Participants will be reminded of their follow-up visit by telephone in advance of their visit. In order to minimize attrition, in particular participants from the control group, a fixed amount of monetary reward will be provided to those who completed all assessments.

### Phase 3 – evaluation of the intervention

#### Process evaluation

We will include brief self-report measures at data collection sessions to gauge participants’ views of the acceptability of the intervention components and the intervention itself as well as measures of behavioral and psychological variables. This will provide useful data on the level of intrusion experienced by the participants and an indication of its acceptability. Questionnaire measures of planning will also provide evidence of compliance. In addition, we will conduct a content analysis of the scripts of the audio files recorded during the telephone-delivered intervention sessions, in order to confirm their compliance with the intervention. This will permit the formal evaluation of intervention fidelity. As part of the fidelity checks and to minimize the potential influence of contamination and spill-over, we will ask participants whether they are aware of any eligible participants from the other intervention or control groups are their friends they interacted with, whether they have enrolled in some influenza prevention classes offered by their centers, as well as whether they are aware of any special effort has been provided by the center to promote influenza prevention in the period of intervention. In addition, we will encourage participants not to share their experiences with other potential participants. Moreover, we will track the impact of the influence of the potential new pandemic if any by asking participants their awareness and feelings.

#### Outcome evaluation

Psychological data will be collected at an isolated room provided by the elderly center during the baseline, the 3-month (the middle time point of intervention), the 6-month (post-intervention), and the 12-month follow-up occasions, whereas the three influenza prevention behaviors variables (i.e., washing hands, avoid touching eyes, nose or mouth, and facemask wearing) and vaccination will be collected via telephone calls in three randomly-selected days in nine. Participants’ self-reported clinical influenza episodes as well as flu-like symptoms during the past 3 months will also be collected.

#### Data analysis

Data will be stored in password-protected spreadsheets saved on a computer of a member of the research team. Data will be initially treated for missing values with multiple imputation. The distribution of the data will be examined that the skewed data will be log-transformed and replaced with median (interquartile range). All analyses will be conducted using full intention-to-treat analyses with scores on dependent variables for non-compliers carried over using the last-observation carried forward method. Independent samples t-tests and chi-square analysis will be used to test whether there are significant differences between non-compliers and compliers. We will analyze the effectiveness of the intervention using a series of linear mixed models on each behavioral and psychological outcome variable. In the analyses, four phases will be the within-participants factor and three intervention conditions will be the between-participants factor. Baseline scores for the dependent variables will be included as covariates in the analysis with salient demographic variables: age, gender, marital status, education level, and socioeconomic status. We will use Akaike and Bayesian information criteria to assess whether a compound symmetry covariance structure will provide the best model fit of each outcome variable. The phase (i.e., time of measurement) by intervention condition (i.e., behavior initiation + behavior maintenance; behavior initiation only; and control group) interaction will be the central test. Beyond main effects of the intervention, we will also test whether there are any statistically significant interactions between the intervention condition and the time factor. For all tests, the Cohen’s d effect size will be calculated associated with a 95% confidence interval. Structural equation modelling (SEM) will be used to test the hypothesized theoretical sequence in the HAPA model [25]. In the analyses, the effect of the intervention group conditions will be included using a dummy coded variable along with the demographic and baseline variables. The 95% bias corrected (BC) bootstrapping method (with *n* = 5000 bootstrap resamples) was subsequently employed to test the indirect effects of mediators (e.g., intention, maintenance and recovery self-efficacy, action and coping planning) (25). The CONSORT Extension for Nonpharmacological Treatment Interventions will be followed to report the results.

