### Design

This project will be conducted in three phases over 24 months in a sample of older adults from Hong Kong. Phase 1 (Months 1 to 4) – Development of intervention using the HAPA theory and preparation for data collection including participant recruitment and preparation of materials and measures. Recruitment will overlap with Phase 2 until the required sample size has been recruited. Phase 2 (Months 4 to 20) – Implementation of the intervention including baseline measures, intervention administration through telephone, ongoing follow-up outcome (See Fig. 1). Phase 3 (Months 21 to 24) – Evaluation of intervention through: (a) evaluating the immediate impact through effects on outcomes at 6-month post-intervention; (b) evaluating the long-term impact of the intervention through effects on outcomes at 12-month follow up; and (c) assessing the compliance of the participants with the intervention.

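### Multiple imputation and LOCF for undefined non-compliers are both prescribed, with no scope or order of priority, in analyses labelled intention-to-treat

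*Protocol article*

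**What the plan says.** The Data analysis section of the protocol article sets two rules in the same paragraph. The first is "Data will be initially treated for missing values with multiple imputation". The second follows shortly after: "All analyses will be conducted using full intention-to-treat analyses", with "scores on dependent variables for non-compliers carried over using the last-observation carried forward method". The effect of the intervention is then estimated "using a series of linear mixed models on each behavioral and psychological outcome variable", and the time-by-condition "interaction will be the central test".

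Non-complier is not defined there. Elsewhere, compliance refers to following the intervention. The Design section lists "assessing the compliance of the participants with the intervention" among the evaluation tasks, and Process evaluation uses the audio recordings of the sessions for the same purpose. For the third arm, the section on the initiation sessions says "Participants in the control group will not receive the telephone-delivered intervention sessions".

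On dropout, the Sample size section allows for 25% attrition overall. Follow-up measures pays a reward to those who complete all assessments, introduced by "In order to minimize attrition, in particular participants from the control group". Visits are at baseline and at 3, 6 and 12 months. Six-month sustainability of the effect is a stated objective.

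**The concern.** Two analysts following this paragraph could build different datasets. Once imputation is complete, no outcome value is missing, so a later LOCF step has nothing to fill. It can only replace values, whether imputed or measured. If non-complier keeps the meaning it has elsewhere in the article, LOCF would replace real follow-up scores of people who skipped sessions. It could do so only in the two intervention arms, because controls have no sessions to skip.

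If LOCF is instead the rule for dropouts, it fixes each of them at the last observed level. Someone lost after the 6-month visit stays at the post-intervention level at 12 months, which is where relapse would show. As a single imputation, it also enters carried scores as though they had been measured. The rule applies to all analyses, so the central test and every behavioral and psychological outcome depend on it.

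**Working it through.** **The plan's own figure.** 65 per group at follow-up with 25% attrition gives 65 / (1 − 0.25) = 86.7, so 87 per group and 3 × 87 = 261. This reproduces the Sample size section. About 22 of 87 people per arm could therefore lack a 12-month score.

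**Assumptions for what follows.** The article gives no trajectories, no correlation between visits and no dropout pattern. I assume SD 1, a correlation of 0.5 and, unless stated otherwise, dropout unrelated to outcome.

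**Reading A: LOCF replaces scores of people who did not follow the sessions.** Only the intervention arms are affected. If a share q is carried back to baseline, a true effect of 0.20 becomes 0.20 − q × (common trend + 0.20). With q = 0.25:
- no common trend: 0.20 − 0.25 × 0.20 = 0.15
- common improvement of 0.3: 0.20 − 0.25 × 0.50 = 0.075
- common decline of 0.3: 0.20 − 0.25 × (−0.10) = 0.225

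**Reading B: LOCF fills in for dropouts.** Take 25% dropout in each arm at a constant hazard after each of the first three visits: h = 1 − 0.75^(1/3) = 0.0914. The shares last seen at baseline, 3 and 6 months are then 0.091, 0.083 and 0.075. Expected 12-month differences under LOCF are:
- effect 0.4, 0.2, 0 at 3, 6, 12 months (full relapse): 0.083 × 0.4 + 0.075 × 0.2 = 0.05, where the truth is 0
- sustained effect of 0.20: 0.20 × (1 − 0.091) = 0.18
- effect 0.4, 0.3, 0.2: 0.083 × 0.4 + 0.075 × 0.3 + 0.75 × 0.2 = 0.21, almost unbiased

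A large simulation (200,000 per arm) gave 0.05, 0.18 and 0.21 under LOCF. Regression imputation recovered the truth in each case.

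**Unequal dropout with no true effect.** Both arms improve by 0.3. With 15% dropout in the intervention arm and 35% in controls, LOCF gives +0.02 if dropout is unrelated to outcome and +0.08 if it depends on the last observed score. With the rates reversed the figures are −0.02 and −0.07. Imputation stays at about 0 throughout.

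**Extreme case.** If everyone who drops out leaves straight after baseline, the null bias is (control attrition − intervention attrition) × common rise. At 35% against 15% and a rise of 0.5, this is 0.20 × 0.5 = 0.10. Simulated with 87 per arm and a two-arm 12-month ANCOVA, false positives are about 13% at alpha 0.05 and about 6% at the article's 0.017. A time-by-condition test in the same scenario rejects about 9 to 11% of the time at 0.05. If the last visit is instead spread evenly over baseline, 3 and 6 months, with the rise complete by 3 months, only a third of dropouts are carried at baseline. The bias falls to 0.10 / 3 = 0.03, and rejection at 0.05 is about 6% with either test.

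**The case against.** The two rules can be reconciled. Imputation may be meant for isolated gaps and LOCF for people who leave. The next step in the article, a comparison of compliers with non-compliers, resembles a routine attrition check. Controls having no sessions to comply with also makes the dropout reading plausible. This objection stands in part: the text is ambiguous, and overwriting observed scores is one possible reading, not a declared plan. It does not rescue the rule, because the text does not state this division and LOCF would still govern dropout in every analysis.

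A reader might infer that LOCF is sure to create or inflate an intervention effect, since the article singles out control attrition. The documents do not support that. They name controls in connection with a completion reward meant to limit attrition, give no expected difference between arms, and use one 25% rate. The 35/15% split is an assumption, and reversing it reverses the sign. The 0.10 SD and 13% figures also depend on every dropout leaving right after baseline, on alpha 0.05 where the article states 0.017, and on a 12-month ANCOVA in place of the time-by-condition test.

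The near-floor baseline follows from eligibility for the behaviors screened at entry. It does not extend to the psychological outcomes.

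**Conclusion.** The point holds as a badly fixed rule. The article itself prescribes both methods, so this is not detail left to an analysis plan. As written, the two rules conflict, or at best leave open which values each one governs. One available reading departs from intention-to-treat, and the other rests on an assumption of no change after the last visit that sits badly with a sustainability objective and a time-by-condition test.

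That LOCF biases the result by a known amount or in a known direction is not established. In the dropout scenarios the bias ranged from near zero to about 0.08 SD, up to 40% of the planned 0.20 (0.08 / 0.20), and could take either sign. The value of 0.10 SD is an extreme case. All these sizes rest on assumed trajectories, correlation and dropout patterns. The ambiguity between the two rules depends on none of them. I put no separate figure on the understated uncertainty.

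**What to change.** - Delete LOCF as the primary rule. If it is kept at all, label it a sensitivity analysis.
- Define non-compliance with the sessions separately from a missing outcome, and say what non-compliance means, if anything, in the control arm.
- State that everyone is analysed as randomised with every observed score, whatever their session attendance.
- Name one primary method valid under missing at random: the planned linear mixed model on the incomplete records, or multiple imputation by arm using baseline and all visits. Do not use both.

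A missing-not-at-random check would be useful, but it is optional and can be left to the statistical analysis plan. The cost is a few sentences in the Data analysis section. The sample size and data collection do not change.

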## Methods

### Participants

Participants in the current study will comprise Hong Kong Chinese older adults. Participants will be eligible if they are 65 years or over; retired or homemakers; willing to be randomly assigned to experimental or control groups; able to understand the study rationale; a first-language Cantonese-speaker; and, most importantly, non-vaccinated within 1 year and report never or rarely adopting any of the influenza prevention behaviors listed by the research group. Participants who report more frequent preventive behaviors will not be invited to attend the preliminary session. We will also exclude older adults who are dementia as well as who are fragile to move.

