#### Control group

Participants randomly assigned to the control group will not receive the behavior-change components of the telephone-delivered intervention sessions. Indeed, participants in the control group will receive some general information on influenza prevention in the group-delivered preliminary session. But, the behavior-change aspects of the information-giving component, goal-setting, mental-simulation, and implementation intention components will be absent from the control group as they will not receive the telephone-delivered intervention sessions. The part-time research assistants will be provided with training and a feedback session to ensure consistency in delivering the intervention.

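### Behavioural outcomes go into linear mixed models with a covariance that reads as shared by all three arms, so the standard error for hypothesis (b) is probably moderately too small

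*Protocol article*

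**What the plan says.** All from the protocol article.

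- **Model (Data analysis).** "We will analyze the effectiveness of the intervention using a series of linear mixed models on each behavioral and psychological outcome variable". The behavioural outcomes include vaccination, which the aims list as a primary outcome and which Follow-up measures records as whether the participant was vaccinated.
- **Covariance (Data analysis).** Akaike and Bayesian criteria are used to "assess whether a compound symmetry covariance structure will provide the best model fit of each outcome variable". The structure is considered outcome by outcome. The text does not mention parameters that differ by arm, or robust standard errors.
- **Tests.** The phase-by-condition "interaction will be the central test". Hypothesis (b) is nevertheless a separate pairwise claim, initiation + maintenance against initiation only. The Sample size section sets alpha at .017, given as .05/3.
- **Entry (Participants).** Participants must be unvaccinated within the past year and "report never or rarely adopting any of the influenza prevention behaviors listed by the research group".
- **Control (Control group).** Controls "will not receive the behavior-change components of the telephone-delivered intervention sessions", although "participants in the control group will receive some general information on influenza prevention in the group-delivered preliminary session".

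**The concern.** A linear mixed model with one set of covariance parameters assumes that the spread of the outcome is the same in every arm. For a bounded outcome the spread depends on the mean. It is small near zero and grows as the mean moves towards the middle of the scale. The entry rule puts all arms near zero, and hypothesis (a) expects the two active arms to move up relative to control. The control arm would then be the low-variance arm.

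A pooled variance is an average over the three arms. For the comparison of the two active arms it is pulled down by a control arm that takes no part in that comparison, so the interval is too narrow. For active versus control it is too large, and power is lost. Hypothesis (b) is the question that the third arm was added to answer. A false claim that the maintenance calls add something is therefore the error at stake.

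Choosing between correlation patterns over time by information criteria does not deal with this, unless structures that differ by arm are among the candidates.

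**Working it through.** **Inputs from the documents.** Three equal arms, 65 per arm at follow-up, alpha .05/3 = .0167 (Sample size). The stated recruitment figure reproduces: 65/(1 − .25) = 86.7, rounded up to 87, and 3 × 87 = 261. The plan gives no arm rates, standard deviations or standard errors, so there is no figure of its own to reproduce on this point.

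**Assumptions.** Two-sided testing (z = 2.394). A binary outcome such as vaccination, with variance m(1 − m). The same rate in both active arms, so that hypothesis (b) is null. The control and active rates are illustrative.

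**Formulas.** Let q = control variance / active variance.

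1. With equal arms, the pooled variance has expectation (active variance) × (2 + q)/3.
2. Active v active: used SE / correct SE = sqrt((2 + q)/3).
3. Active v control: used SE / correct SE = sqrt(2(2 + q) / (3(1 + q))).
4. Actual type I error = 2 × P(Z > 2.394 × ratio).

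**Worked case, 10% v 30%.** q = (.10 × .90)/(.30 × .70) = .09/.21 = .429. The active v active ratio is sqrt(2.429/3) = .900, and 2 × P(Z > 2.394 × .900) = 3.1%. The active v control ratio is sqrt(4.857/4.286) = 1.065, giving 1.1%.

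| Control v active (assumed) | d on this scale | q | SE ratio, active v active | Type I error, hypothesis (b) | SE ratio, active v control | Type I error, active v control |
|---|---|---|---|---|---|---|
| 10% v 17% | .21 | .638 | .938 | 2.5% | 1.036 | 1.3% |
| 10% v 30% | .52 | .429 | .900 | 3.1% | 1.065 | 1.1% |
| 10% v 40% | .74 | .375 | .890 | 3.3% | 1.073 | 1.0% |

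Here d = (active rate − control rate) / sqrt(mean of the two variances).

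**Simulation check.** Binary outcome at one visit, 65 per arm, variance pooled over arms. Type I error for hypothesis (b) was 2.5%, 3.2% and 3.5% in the three rows. With variances taken from the two arms compared, it was 1.6%, 1.7% and 1.7%. The formula and the simulation agree.

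**When the nominal rate doubles.** This needs q of about .37 or less (control SD / active SD of about .61). With control at 10%, q is smallest at an active rate of 50%: .09/.25 = .36, giving 3.4%. So with control at 10% the error roughly doubles at worst. A control rate of 5% against 30% (q = .0475/.21 = .226) gives 3.9%.

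**When the bias disappears.** q returns to 1 when the active rate equals one minus the control rate. For control at 10% and active at 90%, both variances are .09 and there is no bias. Above that point the direction reverses.

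**The case against.** The strongest reply is that the article nowhere says the arms share a covariance. It names a structure and a selection criterion, and grouped covariance or robust errors are details that a statistical analysis plan may settle. It stands that sharing is an inference. But the article does choose the model class and says how its covariance will be judged, outcome by outcome. A compound symmetry structure without qualification ordinarily means one set of parameters for all participants. That choice fits poorly with the trial's own entry rule and first hypothesis.

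Other points that stand:

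- **Controls may not stay at the floor.** They receive the education session, are telephoned repeatedly about their behaviour, and were selected for low values, so some rise is likely. Hypothesis (a) requires only that the active arms exceed them. This raises q and reduces the bias.
- **The variance formula is not universal.** Avoiding touching the face is asked as a number of times, to which m(1 − m) does not apply. The planned log-transformation of skewed data can narrow the variance gap for such outcomes or reverse it. It cannot change the ratio for a yes/no outcome.
- **The central test is the omnibus interaction.** The figures above describe a pairwise contrast at a single visit, without covariates, imputation or carried-forward values.

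A reader might infer that the false-positive rate for hypothesis (b) is at least doubled, or that the bias always grows as the intervention works better. The documents support neither. At 10% v 17%, near the planned d = .20, the inflation is about 1.5 times. Since m(1 − m) peaks at 50%, a stronger effect beyond that point reduces the bias.

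**Conclusion.** The point holds in a conditional and moderate form. If the covariance is shared by the arms, as the text ordinarily reads, and active rates stay at or below about 50% with control lower, the hypothesis (b) standard error is too small by roughly 6% to 11% in the cases shown. Its type I error is then about 2.5% to 3.5% against a nominal 1.67%. Active versus control is somewhat conservative under the same conditions.

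The direction rests on the documented entry floor and hypothesis (a). The size rests on assumed arm rates. The conclusion applies to the behavioural outcomes and most firmly to vaccination. It does not extend to the psychological outcomes, for which no floor is documented. The error rate of the phase-by-condition test was not computed.

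**What to change.** In Data analysis, state for the behavioural outcomes that the covariance parameters may differ by intervention condition. Alternatively, state that standard errors will be cluster-robust by participant with a small-sample correction. Take the three pairwise contrasts, including hypothesis (b), from that model.

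The cost is a sentence in the plan, a software option and a few more variance parameters. The power loss at 65 per arm is negligible. If the arms turn out to have equal variances, the results will hardly change.

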### Phase 2 – implementation of the intervention

#### Sample size

We will assume a small effect size (Cohen’s *d* = .20) for the effect of the intervention in order to calculate a conservative post-intervention sample size sufficient to detect an effect. G*Power analysis using the between-factor (i.e., 3 groups) repeated measures (i.e., 4 phases; baseline, 3-month, 6-month, and 12-month measurements) multivariate analysis of variance (MANOVA) indicates that a sample size of 65 in each group is required at follow-up in order to detect a small effect size (*d* = .20) in the outcome variables with power (beta) set at .90 and significance level (alpha) set at .017 (i.e., .05/3). Based on conservative estimate of 25% attrition rates, we aim to recruit 261 participants at baseline (*n* = 87 participants per group).

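### Baseline is both one of the four outcome phases and a covariate, so the central interaction test is an unadjusted change-from-baseline comparison: valid, but not the adjusted analysis described

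*Protocol article*

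**What the plan says.** The Data analysis section plans linear mixed models for each behavioural and psychological outcome, in which "four phases will be the within-participants factor and three intervention conditions will be the between-participants factor". It does not name the four phases there, but the Sample size section does: "4 phases; baseline, 3-month, 6-month, and 12-month measurements". Baseline is thus one of the outcome occasions. The Data analysis section then adds: "Baseline scores for the dependent variables will be included as covariates in the analysis", together with demographic variables.

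On testing, the phase-by-condition "interaction will be the central test". Main effects are also tested: "Beyond main effects of the intervention, we will also test whether there are any statistically significant interactions". Cohen's d with a 95% confidence interval is promised for every test. Information criteria are to show "whether a compound symmetry covariance structure will provide the best model fit of each outcome variable". The article does not restrict the outcomes to post-baseline visits, add a baseline-by-phase term or constrain the arms to equal baseline means.

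**The concern.** At the baseline phase the outcome is its own covariate. The plan therefore describes an adjusted analysis whose adjustment may not reach the test that matters. A reader of the results would take the interaction as baseline-adjusted, with the precision that adjustment usually brings, when it is a comparison of raw changes. In addition, a condition effect averaged over four phases includes one at which no intervention effect can exist, so the reported effect size would be too small. At stake are the precision of the central test and the correct reading of the published estimates.

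**Working it through.** **Inputs from the protocol article.** Four phases including baseline, three arms, baseline score as covariate, alpha .017, and 65 per group at follow-up (Sample size and Data analysis sections). The article gives no figure for the effect of baseline adjustment, so there is none to reproduce. The recruitment target follows from the 65: 65/(1 − .25) = 86.7, rounded up to 87, and 3 × 87 = 261. The 65 is used below only as the arm size of the illustrations.

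**Assumed, not in the article.** r, the correlation of baseline with follow-up; k, the baseline SD divided by the follow-up SD; and the effect sizes in the simulations and the power comparison.

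**1. The covariate cancels from the interaction.** Write the model for person i at phase t as Y(i,t) = phase + arm + phase × arm + b·Y(i,0) + person effect + error. In any within-person contrast Y(i,t) − Y(i,0), the term b·Y(i,0) appears twice with opposite sign and drops out. The interaction has (4 − 1) × (3 − 1) = 6 degrees of freedom. On a simulated complete dataset (65 per arm, random intercept):

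| | Without baseline covariate | With it |
|---|---|---|
| 6-df Wald statistic | 32.88 | 32.88 |
| 12-month coefficient, first active arm | 0.348 | 0.348 |
| 12-month coefficient, second active arm | 0.902 | 0.902 |
| Standard error | 0.175 | 0.175 |

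All six coefficients and standard errors agree, and each coefficient equals the raw between-arm difference in change from baseline (0.348 and 0.902 at 12 months).

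**2. What the missing adjustment costs at one visit.** In units of the follow-up variance:

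- change score: 1 + k² − 2rk
- baseline-adjusted (ANCOVA): 1 − r²
- ratio: (1 + k² − 2rk)/(1 − r²)

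| | r = .2 | r = .3 | r = .5 | r = .7 |
|---|---|---|---|---|
| k = 1 | 1.67 | 1.54 | 1.33 | 1.18 |
| k = .7 | 1.26 | 1.18 | 1.05 | 1.00 |
| k = .5 | 1.09 | 1.04 | 1.00 | 1.08 |

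For example, at k = 1 and r = .5 the ratio is (2 − 1)/(1 − .25) = 1.33; at k = .5 and r = .3 it is (1.25 − .30)/.91 = 1.04.

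**3. Like-for-like power where k = 1.** To separate the adjustment from the choice of hypothesis, both sides are 6-df joint tests (asymptotic, 65 per arm, alpha .017, the same effect in both active arms at all three follow-ups).

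| Assumed effect | r | Change from baseline | Baseline-adjusted |
|---|---|---|---|
| 0.4 SD | .3 | .33 | .75 |
| 0.4 SD | .5 | .50 | .78 |
| 0.4 SD | .7 | .80 | .92 |
| 0.2 SD | .3 | .06 | .14 |
| 0.2 SD | .5 | .09 | .15 |
| 0.2 SD | .7 | .16 | .23 |

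These are the equal-variance case and shrink with k as in step 2.

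**4. The averaged main effect.** The four-phase mean is (Y0 + 3 × mean follow-up)/4. Given Y0, the arm effect on it is 3/4 of the mean follow-up effect. In the simulated dataset, without interaction terms:

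| | Four phases | Three follow-ups | Ratio |
|---|---|---|---|
| First active arm: estimate (SE) | 0.266 (0.0814) | 0.355 (0.1085) | 0.75 |
| Second active arm: estimate (SE) | 0.509 (0.0814) | 0.679 (0.1085) | 0.75 |
| t values | 3.27 and 6.26 | 3.27 and 6.26 | 1.00 |

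Estimate, interval and any Cohen's d built on them shrink by a quarter; the test does not change.

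**The case against.** The best defence is that nothing invalid results. Under randomisation a change-from-baseline comparison is unbiased, and the redundant covariate does that test no harm. This stands: the point concerns efficiency and correct description, not error rates.

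Three stronger readings are tempting, and the documents do not support them.

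- *The entry criterion of never or rarely adopting the behaviours lowers r, so the loss is greatest there.* The same restriction would be expected to shrink baseline variance too. With k about .5 the ratio is near 1, so the argument works against a large loss for the behaviours. Vaccination within the past year is an exclusion, so it has no baseline variation to adjust for. The larger ratios are more plausible for the psychological outcomes, which are not entry criteria.
- *The diluted main effect costs power.* Estimate and standard error shrink together. The 0.75 also depends on coding: with baseline as the reference phase and the interaction in the model, the condition term is the baseline difference, and the interaction coefficients are undiluted.
- *The trial is already short of power.* The 65 per group depends on a between-visit correlation that the article does not give, so this cannot be concluded from the present point.

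It can also be said that a single common slope and compound symmetry are not firmly fixed: the article is silent on a baseline-by-phase term, and the covariance structure is to be checked by information criteria. That limits the exact cancellation to the model as written. It does not remove the double use of baseline, which both sections state outright.

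**Conclusion.** The concern holds in a limited form. As described, baseline is at once outcome and covariate, and the adjustment contributes nothing to the central test, which becomes a valid but unadjusted change-from-baseline comparison. This is exact for a common baseline slope, compound symmetry and complete or imputed data.

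The price is a per-visit variance 1.18 to 1.54 times that of the baseline-adjusted analysis for r from .7 to .3 with equal variances, and about 1.00 to 1.09 for r from .2 to .7 when k is .5. Both r and k are assumptions. A condition effect averaged over four phases understates the mean post-baseline effect by exactly a quarter, in the estimate, interval and Cohen's d, without changing its significance. The finding does not show bias or an inflated error rate in the central test.

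**What to change.** State one role for baseline, in either of two ways.

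- **Baseline as covariate.** Model only the 3-, 6- and 12-month visits, with baseline and baseline-by-phase as covariates. The central test must then be redefined as baseline-adjusted arm contrasts by visit, or a joint test of them. Without baseline among the outcomes, phase-by-condition tests only whether the effect differs between 3, 6 and 12 months (4 df instead of 6; the statistic in the simulated dataset was 9.29 instead of 32.88).
- **Baseline as outcome.** Keep all four visits, drop the baseline covariate, constrain the arm means to be equal at baseline and use an unstructured covariance. The phase-by-condition contrasts then remain the central test.

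In both, report any average effect and its Cohen's d over the post-baseline visits only. The cost is rewording the Data analysis section, including the central test in the first option, and estimating a few more parameters. No new data are needed.
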